##### **3.1.1. Part A: Single-Ascending Dose [SAD] (Cohorts 1-5)**

Part A will evaluate the safety, tolerability, PK, and PD of single-ascending doses of oral TLC-2716 or placebo under fed conditions. Part A will proceed in up to 5 dose-escalation cohorts and will be governed by a review of safety, tolerability, and any available and relevant PK and/or PD data, and study-specific stopping criteria. Planned study treatments within each cohort are provided in [Table 2](#).

- Within each cohort, 10 unique subjects will be randomized 4:1 to receive either blinded TLC-2716 (N = 8) or PTM (N = 2). All study drugs in Part A will be administered in the morning following a standard meal.
- At the initiation of each cohort in Part A, prior to randomization of the entire cohort, two sentinel subjects will be randomized, one to TLC-2716 at the dose to be evaluated in the planned cohort, and one to corresponding PTM. Enrollment and randomization of the remaining eight subjects in each cohort will be determined upon evaluation of all safety and tolerability data through Day 2 for these two sentinel subjects.
- For cohorts 2-5, initiation of single-dose administration will be permitted after evaluation of cumulative blinded safety data, and any relevant and available PK and/or PD data up to and including Day 4, following single-dose administration of the previous cohort.

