**Table 2. Treatments to be Administered in Cohorts 1-5**

| Cohort | Single Ascending Doses (Day 1)                                           |
|--------|--------------------------------------------------------------------------|
| 1      | 0.5 mg TLC-2716 (1 x 0.5 mg) or PTM capsule SD, fed                      |
| 2      | 2 mg TLC-2716 a (1 x 2 mg) or PTM capsule SD, fed             |
| 3      | 6 mg TLC-2716 a (3 x 2 mg) or PTM capsules SD, fed            |
| 4      | 12 mg TLC-2716 a (2 x 5 mg; 1 x 2 mg) or PTM capsules SD, fed |
| 5      | 20 mg TLC-2716 a (4 x 5 mg) or PTM capsules SD, fed           |

PTM = placebo-to-match; SD = single dose

a The planned doses may be modified based on the observed safety, tolerability, and any relevant and available PK and/or PD data. Any modified dose will be within 3-fold of a dose previously tested.

A schematic of the activities within Part A cohorts is shown in [Figure 1](#). Adaptive SAD cohorts in Part C will follow the same study schema.

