### **8.7. Pharmacokinetic Analysis**

Plasma concentrations and PK parameters (e.g.,  $AUC_{last}$ ,  $AUC_{inf}$  [single-dose],  $\%AUC_{exp}$  [single dose],  $CL/F$  [single dose],  $AUC_{tau}$  [multiple-dose],  $C_{tau}$  [multiple-dose],  $CL_{ss}/F$  [multiple dose], and  $V_z/F$ ,  $C_{max}$ ,  $T_{max}$ ,  $C_{last}$ ,  $T_{last}$ ,  $\lambda_z$ ,  $CL/F$ , and  $t_{1/2}$ , if applicable) will be listed and summarized for TLC-2716 (and its metabolites, as applicable) using descriptive statistics by treatment for each cohort.

Dose proportionality will be assessed by comparing PK parameters of TLC-2716 across evaluated dose levels. A power model will be fitted using all doses across cohorts to evaluate the dose proportionality based on  $AUC_{last}$ ,  $AUC_{inf}$  (single-dose),  $AUC_{tau}$  (multiple-dose),  $C_{tau}$  (multiple-dose), and  $C_{max}$ . The population mean slope will be estimated with a 90% confidence interval. An alternate evaluation of dose proportionality may be conducted using analysis of variance (ANOVA) on dose normalized, natural log-transformed AUC,  $C_{tau}$  (multiple-dose), and  $C_{max}$ . Dose proportionality analyses will be conducted separately for the single- and multiple-dose cohorts.

Additional analyses such as accumulation ratio and time to steady state may be conducted as appropriate. If fasted cohorts are conducted in Part C, an evaluation of the effect of fasting status on TLC-2716 PK may be conducted.

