#### **8.1.4. Pharmacokinetic Statistical Analyses**

##### **8.1.4.1. Dose Proportionality**

Dose-proportionality of plasma TLC-2716 and its metabolites, PK parameters,  $C_{\max}$ ,  $AUC_t$ ,  $AUC_{\text{tau}}$ , and  $AUC_{\text{inf}}$ , as applicable for Part A, Part B, and Part C (as applicable) over the dose range tested will be investigated. A power regression model will be fitted to describe the relationship between Y ( $C_{\max}$ ,  $AUC_{\text{tau}}$ ,  $AUC_{\text{last}}$ , and  $AUC_{\text{inf}}$ ) and X (dose) under fasting conditions. The model is defined as:

$$\ln(Y) = \beta_0 + \beta_1 \ln(X), \text{ where Y is PK parameter and X is dose}$$

The null hypothesis that will be tested is that the AUCs and  $C_{\max}$  values are dose-proportional, or slope  $\beta_1=1$  is within 90% CI of the slope.

An alternative evaluation of dose proportionality may be conducted using analysis of variance (ANOVA) on dose normalized, natural log-transformed AUC and  $C_{\max}$  of TLC-2716 and its metabolites. The model will include dose as a fixed effect. The two-sided 90% CI for the ratio of dose comparisons will be constructed.

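### The SAP's dose-proportionality test has no margin and makes proportionality the null hypothesis, so noisy data can favour a finding of proportionality when it is false

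*Combined protocol and SAP*

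**What the plan says.** Protocol 8.7 treats dose proportionality as estimation. A power model is fitted across doses, separately for single- and multiple-dose cohorts, and "The population mean slope will be estimated with a 90% confidence interval". It gives no acceptance rule and no margin.

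SAP 8.1.4.1 keeps the model ("A power regression model will be fitted to describe the relationship between Y" and dose, on log scales) but adds a test. In its words, "The null hypothesis that will be tested is that the AUCs and" Cmax values are dose-proportional, which it restates as the condition that a slope of 1 "is within 90% CI of the slope". That is the only criterion in the section. For the optional ANOVA on dose-normalised values, "The two-sided 90% CI for the ratio of dose comparisons will be constructed", with no limits and no decision attached.

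Each Part A and Part B cohort randomises ten subjects to "receive either blinded TLC-2716 (N = 8) or PTM (N = 2"). The planned doses are 0.5, 2, 6, 12 and 20 mg. Protocol 8.10 states that there was no reliable variability estimate and no formal sample size calculation.

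**The concern.** A slope interval that contains 1 shows only that the data do not rule out proportionality. It does not show that the slope is near 1. A criterion built this way has two faults.

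- If exposure is truly non-proportional, a wider interval is more likely to cover 1, so poor precision favours the finding of proportionality.
- If exposure is exactly proportional, a 90% interval covers 1 in 90% of trials at any sample size, so good precision brings no benefit. With precise data, the same rule rejects departures that may be too small to matter.

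Pharmacokinetic characterisation is a primary objective, and protocol 1.3 says the study's results will inform dose selection for Phase 2. A report that calls exposure dose-proportional on this criterion could be carried forward as a finding when it reflects imprecision. Protocol 1.2.3 describes low systemic exposure and undetectable plasma levels 2-4 hours after dosing in preclinical work. Variable low-dose AUCs are therefore plausible, though the documents give no figure for humans.

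**Working it through.** The plan states no power, precision or margin for this analysis, so there is no figure of its own to reproduce.

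**Inputs.** From the protocol: doses 0.5, 2, 6, 12 and 20 mg (Tables 2 and 3); 8 active subjects per dose (3.1.1 and 3.1.2); separate single- and multiple-dose fits (8.7). Each fit therefore has N = 5 × 8 = 40, with r = 20/0.5 = 40. Assumed: between-subject CV from 20% to 100%, lognormal and equal across doses. I take the fed Part A or Part B cohorts as the data. SAP 8.1.4.1 refers to fasting conditions, which does not fit these fed cohorts and needs separate reconciliation.

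**Spread of log dose.** The mean of ln(dose) is 1.454. The squared deviations are 4.612, 0.580, 0.114, 1.062 and 2.375, which sum to 8.743. Hence Sxx = 8 × 8.743 = 69.94. Degrees of freedom are 38 and t(0.95) = 1.686.

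**Precision.** Residual SD σ = √ln(1 + CV²); SE(slope) = σ/√69.94; half-width of the 90% interval = 1.686 × SE.

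**True slope for a given shift.** If dose-normalised exposure changes f-fold over the range, the slope is 1 + ln(f)/ln(40).
- f = 2: 1 + 0.693/3.689 = 1.188
- f = 1.25: 1 + 0.223/3.689 = 1.060

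**Chance that 1 lies inside the interval.** This is P(|T| < 1.686), where T is noncentral t with 38 df and noncentrality (slope − 1)/SE. Example at CV 100%: σ = √ln 2 = 0.833, SE = 0.833/8.363 = 0.0995, noncentrality = 0.188/0.0995 = 1.89, probability 42%.

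| CV (assumed) | SE | Half-width | Criterion met, true 2-fold shift | Criterion met, exact proportionality |
|---|---|---|---|---|
| 20% | 0.024 | 0.040 | about 0% | 90% |
| 30% | 0.035 | 0.059 | about 0% | 90% |
| 40% | 0.046 | 0.078 | 1% | 90% |
| 60% | 0.066 | 0.112 | 13% | 90% |
| 100% | 0.100 | 0.168 | 42% | 90% |

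**Opposite direction.** At CV 20% with a true 1.25-fold shift, noncentrality is 0.0605/0.0237 = 2.55. The criterion is met about 19% of the time, so proportionality is rejected about 81% of the time.

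**A margin rule for comparison.** Require the whole 90% interval to lie within 1 ± ln(θ)/ln(r). With θ = 2 as an illustration, the limits are 1 ± 0.188, or 0.81 to 1.19. Simulated with the same design, a truly proportional drug passes 98% of the time at CV 40%, 75% at CV 60% and 18% at CV 100%. Under a true shift equal to the limit, the 90% interval holds the pass rate to at most 5% at any CV. Noise now counts against the claim.

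**The case against.** The strongest reply has five parts.

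- **Wording.** The SAP never says that proportionality is accepted or proven; its language is about investigating and describing. This stands. Taking non-rejection as proportionality is the natural reading of the sentence, but it is an unwritten step.
- **Visibility.** The slope and its 90% interval will be estimated, and SAP 8.1.3 summarises geometric means and geometric CVs by cohort, so an alert reader can judge precision. This limits the harm but does not make the stated criterion sound.
- **Variability.** At CV 20-30% a 2-fold shift almost never passes. This also stands: the size of the problem depends on an unknown CV.
- **Smaller shifts.** A reader might count 1.25- and 1.5-fold shifts that pass as misses. That would be inconsistent with a 2-fold margin, under which they are tolerable. At CV 40% a θ = 2 rule passes a 1.5-fold shift 51% of the time, against 24% under the SAP criterion. Whether that is better or worse depends on the margin, and the documents give no basis for choosing one.
- **Consequences.** A reader might infer that this test sets Part C doses. The documents do not support that. Protocol 3.1.3 chooses those doses from available safety, PK and/or PD data. SAP section 10 plans no interim analysis, and protocol 8.2.2 places the final analysis after all subjects finish.

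A reader might also extend the criticism to the optional ANOVA and quote a miss rate for comparing two doses with 8 subjects each. The SAP attaches no decision rule to those ratios, so no such rate applies.

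**Conclusion.** The criterion in SAP 8.1.4.1 is wrong as written. This is a stated rule that can point to proportionality because the data are imprecise, not merely a missing detail.

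The size depends on the assumed CV, the full five-dose range and 8 evaluable active subjects per dose. It is negligible for a 2-fold shift at CV 20-40% and material from about CV 60% upward. At low CV the fault reverses, and small departures over a 40-fold range are usually rejected.

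The documents do not support saying that the SAP declares proof of proportionality, or that any dosing decision within this study depends on the test. The point concerns what the final report may conclude.

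**What to change.** Delete the null-hypothesis sentence from SAP 8.1.4.1. Report the slope β1 with its 90% interval, as protocol 8.7 does. Add r^(β1 − 1), the fold change in dose-normalised exposure over the range analysed, with its 90% interval, where r is the highest dose divided by the lowest dose in that fit.

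If the sponsor wants a categorical conclusion, it should fix θ before the analysis and state three outcomes:
- proportional, only if the whole 90% interval lies within 1 ± ln(θ)/ln(r);
- non-proportional, only if the interval lies wholly outside those limits;
- otherwise inconclusive.

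θ = 2 is an illustration, not a recommendation; the choice is the sponsor's. The limits should be recomputed if the dose range changes.

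Leave the optional ANOVA as estimation. One θ should not be applied to every dose pair. For 20 versus 12 mg, a slope of 1.188 implies a ratio of (20/12)^0.188 = 1.10, so a 2-fold limit would be far looser there than the slope limit.

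The cost is one paragraph of SAP text, with the same model and data. The drawback of a margin is that the result may be inconclusive. With θ = 2, a truly proportional drug would fail to be declared so about 2%, 25% and 82% of the time at CV 40%, 60% and 100% (100% minus the pass rates in the check). Reporting estimates alone avoids this.

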##### **8.1.5. Evaluation of Food Effect**

For statistical evaluation of food-effect, PK parameters ( $AUC_{\text{last}}$ ,  $AUC_{\text{inf}}$ , and  $C_{\max}$ ) of TLC-2716 under fasted conditions versus fed conditions for selected cohort(s) will be compared by ANOVA using a linear mixed effect model with fed/fasted status as a fixed effect and participant as a random effect, unless otherwise stated. The ratio of geometric means and associated 90% CI will also be calculated for  $AUC_{\text{last}}$ ,  $AUC_{\text{inf}}$  and  $C_{\max}$  between the fed and fasted conditions.

##### **8.1.6. Evaluation of Accumulation**

Comparisons between Day 1 ( $AUC_{\text{tau}}$ , and  $C_{\max}$ ) and Day 14 PK parameters ( $AUC_{\text{tau}}$ , and  $C_{\max}$ ) will be performed by ANOVA using the MIXED Procedure for each treatment cohort, with the natural log-transformed values of PK parameters as the dependent variable, study day as the fixed effect, and subject as a random effect, unless otherwise stated. The ratio (Day 14/Day 1) of the geometric least square mean and its corresponding 90% CI will be calculated.

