### 1.2.3. Nonclinical Pharmacokinetics (PK)

Absorption, distribution, metabolism, and elimination of TLC-2716, as well as the potential for drug-drug interactions, were assessed *in vitro* and *in vivo* in preclinical models. The pharmacokinetic (PK) profile indicates limited systemic exposure, with undetectable plasma levels 2-4 hours after dosing, and high levels in the liver consistent with rapid transporter-mediated uptake into hepatocytes.

TLC-2716 is a lipophilic, small molecule, LXR inverse agonist with a high binding affinity to plasma proteins (> 99%) in humans, mice, rats, dogs, and monkeys. Following intestinal absorption into the portal vein, TLC-2716 is highly extracted by the liver (92% hepatic extraction ratio in rats). Consistent with high liver loading, systemic exposure of TLC-2716 was generally low following oral administration in multiple species. In rodents, TLC-2716 was predominantly distributed to the liver and intestine; brain distribution data suggest that little or no TLC-2716-derived compounds cross the blood-brain barrier. *In vitro*, TLC-2716 was stable in primary hepatocytes from human, mouse, and dog. Together with the metabolites observed in

livers from preclinical species *in vivo*, the biotransformation pathway of TLC-2716 appears to involve oxidation, deamination, desulfation, glucuronidation, and taurine conjugation.

In *in vitro* studies, TLC-2716 was not a substrate of CYP1A2, CYP2B6, CYP2C8, CYP2C9, CYP2C19, CYP2D6, or CYP3A5, however, it was a modest substrate of CYP3A4 suggesting that co-administration of CYP3A4 inhibitors or inducers may affect the exposure of TLC-2716. TLC-2716 did not inhibit CYP1A2, CYP2C19, or CYP2D6, but demonstrated weak to modest inhibition of CYP2B6, CYP2C8, CYP2C9, and CYP3A4. In primary human hepatocytes, TLC-2716 induced CYP2B6 and CYP3A4 (> 2-fold relative to control), and therefore, may alter the exposures of co-administered substrates of these CYP enzymes *in vivo*. Finally, inhibition of P-gp, BCRP, OATP1B1, and OATP1B3 by TLC-2716 was observed *in vitro* at 10  $\mu$ M. While these findings suggest that TLC-2716 may alter the exposure of concomitant medications (and vice versa), the unique PK profile of TLC-2716, characterized by minimal systemic exposure and high protein binding, may reduce the potential for clinically relevant drug-drug interactions. Additional studies will be conducted to evaluate the clinical relevance of these findings.

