## **8. PHARMACOKINETIC ANALYSIS**

### **8.1.1. Data Handling**

All PK analyses will use the PK Analysis Set. Plasma concentrations and plasma PK parameters will be listed and summarized for TLC-2716 and its metabolites (TLC-6665, TLC-7255), as applicable using descriptive statistics by treatment and PK Day (as applicable) for each cohort. Plasma concentration versus time curves will also be presented.

Plasma concentrations that are below the limit of quantification (BLQ) will be treated as zero for calculation of descriptive statistics. When all concentrations are BLQ for a timepoint, the mean BLQ concentrations will be presented as BLQ, and the SD and CV will be reported as not applicable.

For PK parameter calculation, BLQ values prior to a quantifiable concentration will be treated as zero. BLQ values between 2 quantifiable concentrations, or in the terminal phase will be set as missing. If consecutive BLQ concentrations in the terminal phase are followed by quantifiable concentrations, those concentrations after consecutive BLQ concentrations will be treated as missing.

No missing data imputation will be performed.

Missing concentrations will be treated as missing from the descriptive statistics and PK parameter calculations.

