### **8.1.2. Plasma Pharmacokinetic Concentrations**

Part A – SAD:

Day 1: Blood samples for PK analysis of concentrations of TLC-2716 and its metabolites in plasma will be collected at the following timepoints: predose ( $\leq 10$  minutes prior to dosing) and 0.25, 0.5, 1, 1.5, 2, 2.5, 3, 3.5, 4, 6, 12, 24, 48, and 72 hours postdose.

Part B – MAD and Part C – Adaptive SAD and/or MAD:

Day 1: Blood samples for PK analysis of concentrations of TLC-2716 and its metabolites in plasma will be collected at the following timepoints: predose ( $\leq 10$  minutes prior to dosing) and 0.25, 0.5, 1, 1.5, 2, 2.5, 3, 3.5, 4, 6, 12, and 24 hours postdose.

Days 3 and 7: Predose ( $\leq 10$  minutes prior to dosing) and 2 and 4 hours postdose.

Day 14: Blood samples for PK analysis of concentrations of TLC-2716 and its metabolites in plasma will be collected at the following timepoints: predose ( $\leq 10$  minutes prior to dosing) and 0.25, 0.5, 1, 1.5, 2, 2.5, 3, 3.5, 4, 6, 12, 24, 48, and 72 hours postdose.

Individual plasma concentrations of TLC-2716 and its metabolites will be presented in data listings and summarized separately using descriptive statistics (N [number of subjects], n [non-missing values within the population], arithmetic mean, SD, CV%, median, minimum, and maximum) by study part, treatment, cohort, day, as applicable, and nominal time point. Mean ( $\pm$  SD) plasma concentrations of TLC-2716 and its metabolites will be plotted by study part, dose, cohort, day, as applicable, and nominal time on both linear and semi-logarithmic scales.

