### 8.1.3. Plasma Pharmacokinetic Parameters

The plasma concentration-time data for TLC-2716 and its metabolites will be analyzed by noncompartmental analysis using Phoenix® WinNonLin® Version 8.3.4 or higher (Certara USA, Inc., Princeton, NJ). The following single- and multiple-dose PK parameters will be calculated for TLC-2716 and its metabolites as applicable based on actual times, where data permit:

| PK Parameter   | Definition                                                                                                |
|----------------|-----------------------------------------------------------------------------------------------------------|
| $C_{max}$      | Maximum observed plasma concentration                                                                     |
| $t_{max}$      | Time of maximum observed concentration                                                                    |
| $t_{last}$     | Time of last measurable concentration                                                                     |
| $AUC_{last}$   | AUC from time 0 to the last quantifiable concentration, calculated using the linear trapezoidal rule      |
| $AUC_{inf}$    | AUC from time 0 extrapolated to infinity, calculated using the linear trapezoidal method                  |
| $AUC_{tau}$    | Area under the concentration-time curve for one dosing interval (tau). (Day 1 and Day 14 for MAD cohorts) |
| $t_{1/2}$      | Apparent terminal elimination half-life, calculated as: $\ln(2) / K_{el}$                                 |
| CL/F           | Apparent total body clearance, calculated as: $Dose / AUC_{inf}$                                          |
| $V_z/F$        | Volume of distribution during the terminal phase, calculated as: $Dose / [K_{el} * AUC_{inf}]$            |
| $AR_{C_{max}}$ | Accumulation ratio based on $C_{max}$ , calculated as: $C_{max} (Day 14) / C_{max} (Day 1)$               |
| $AR_{AUC}$     | Accumulation ratio based on $AUC_{tau}$ , calculated as: $AUC_{tau} (Day 14) / AUC_{tau} (Day 1)$         |

In addition to the above PK parameters, which will be listed and summarized, the following parameters will also be listed to document the selection of data points used to estimate  $t_{1/2}$  using non-compartmental procedures:

| PK Parameter     | Definition                                                                                                                             |

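### The SAP's only formal comparison over time, the Day 14/Day 1 ratio, mixes accumulation with any change in clearance, and the SAP omits the protocol's CLss/F, which would help to separate them

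*Combined protocol and SAP*

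**What the plan says.** SAP 8.1.6 fits a mixed model to log-transformed AUCtau and Cmax in each cohort, with "study day as the fixed effect, and subject as a random effect, unless otherwise stated", and then: "The ratio (Day 14/Day 1) of the geometric least square mean and its corresponding 90% CI will be calculated". The parameter table in SAP 8.1.3 defines AUCtau for "Day 1 and Day 14 for MAD cohorts" and adds the matching individual ratios for AUC and Cmax. It defines CL/F only as dose over AUCinf. It contains neither CLss/F nor Ctau.

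Protocol 8.1.2 lists CLss/F and Ctau for multiple dosing among the primary PK endpoints, and protocol 8.7 repeats them. Protocol 8.7 also allows an optional look at time to steady state, which the SAP does not take up.

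Other information over time is descriptive. SAP 8.1.1 summarises concentrations and parameters "using descriptive statistics by treatment and PK Day (as applicable) for each cohort". SAP 8.1.2 schedules sparse samples ("Days 3 and 7: Predose", then 2 h and 4 h), which are listed and summarised but enter no parameter or model.

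On metabolism, protocol 1.2.3 says of TLC-2716 that "it was a modest substrate of CYP3A4" and that "In primary human hepatocytes, TLC-2716 induced CYP2B6 and CYP3A4", in the latter case more than 2-fold over control.

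**The concern.** A drug that induces an enzyme which clears it can raise its own clearance over two weeks of dosing. Accumulation pushes Day 14 exposure up and induction pushes it down. A single Day 14/Day 1 ratio shows only the net result, so a value near 1 has two readings: little accumulation at constant clearance, or accumulation offset by faster clearance.

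Characterising multiple-dose PK is a primary objective, and the two readings have different consequences for predicting exposure in later studies. The protocol's own parameter for this purpose, CLss/F, is missing from the SAP. The clearance that the SAP keeps, dose over AUCinf, is not a valid clearance after the Day 14 dose if drug has accumulated, because that area includes drug left from earlier doses.

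**Working it through.** The plan states no expected ratio, decision limit or power for this analysis, so there is no figure to reproduce.

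**Inputs from the documents.** Dosing interval τ = 24 h once daily, or 12 h for the twice-daily option in Part C; 8 active subjects per cohort; 90% CI; sampling times as scheduled.

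**Assumptions, because the documents give no values.** One compartment, steady state by Day 14, half-life 4 to 24 h, clearance factor θ (Day 14 over Day 1) of 1.25 to 2, within-subject CV 20% to 40%.

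**Step 1: what the ratio measures.** With k = ln 2/half-life and R = 1/(1 − exp(−kτ)), where R is the accumulation expected at constant clearance:

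- planned ratio AUCtau(Day 14)/AUCtau(Day 1) = R/θ
- time-linearity ratio AUCtau(Day 14)/AUCinf(single dose) = 1/θ, at any half-life

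Once-daily results:

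| Half-life | R | R/θ, θ = 1.3 | R/θ, θ = 1.5 | R/θ, θ = 2 |
|---|---|---|---|---|
| 4 h | 1.02 | 0.78 | 0.68 | 0.51 |
| 6 h | 1.07 | 0.82 | 0.71 | 0.53 |
| 8 h | 1.14 | 0.88 | 0.76 | 0.57 |
| 12 h | 1.33 | 1.03 | 0.89 | 0.67 |
| 24 h | 2.00 | 1.54 | 1.33 | 1.00 |

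The time-linearity ratio is 0.77, 0.67 and 0.50 in every row. Adding first-order absorption (2 per hour, assumed) moved the planned ratio by at most 0.03.

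**Step 2: where the two effects cancel exactly.** Setting R = θ gives half-life = τ ln 2/[−ln(1 − 1/θ)]. Once daily this is 10.3 h (θ = 1.25), 15.1 h (1.5) and 24 h (2). Twice daily it is half of each: 5.2, 7.6 and 12 h.

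**Step 3: what the planned CI would show.** With 8 subjects, SE = σ√(2/8), σ = √ln(1 + CV²), 7 df. At CV 30%, σ = 0.294 and SE = 0.147, so the CI is the estimate ×/÷ 1.32.

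| Half-life, θ | P(planned CI wholly below 1) | P(planned CI includes 1) | P(time-linearity CI wholly below 1) |
|---|---|---|---|
| 4 h, 1.5 | 0.77 | 0.23 | 0.80 |
| 8 h, 1.5 | 0.51 | 0.49 | 0.80 |
| 12 h, 1.5 | 0.18 | 0.81 | 0.80 |
| 24 h, 2 | 0.05 | 0.90 | 0.995 |

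At CV 20% and 40% the last column is 0.98 and 0.60 for θ = 1.5, and 1.00 and 0.94 for θ = 2. It assumes that single-dose AUCinf is well estimated in the same subject, which Step 5 qualifies.

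**Step 4: whether the planned by-day CL/F closes the gap.** At steady state, AUCinf after the Day 14 dose is AUCtau times R at the Day 14 half-life, so the apparent rise in dose/AUCinf is θ/R. At a Day 1 half-life of 24 h and θ = 2, this is 2/1.33 = 1.5 if half-life shortens to 12 h, and 2/2 = 1.0 if half-life does not change. The true rise is 2-fold.

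**Step 5: Day 1 sampling.** Protocol 6.5.1 and both MAD schedules end Day 1 sampling at 12 h; SAP 8.1.2 ends it at 24 h. The share of single-dose AUCinf beyond the last sample is exp(−k × last time), ignoring absorption. At a half-life of 24 h this is 71% at 12 h, 50% at 24 h, and 12.5% at the 72 h used in Part A. Under the 12 h schedule, even Day 1 AUCtau needs extrapolation: at this half-life, (0.707 − 0.5)/0.5 = 41% of it lies after 12 h.

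**Step 6: precision against Part A.** Same dose, 8 versus 8, assumed CV 40%: σ = 0.385, SE = 0.385√(2/8) = 0.193, and with 14 df the 90% CI is ×/÷ 1.40 (1.30 to 1.63 for CV 30% to 60%). If one common ratio is assumed across all five doses, 40 versus 40 gives ×/÷ 1.15.

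**The case against.** The strongest reply is that cancellation needs a half-life that the documents do not suggest. Protocol 1.2.3 reports that in preclinical models plasma drug is no longer detectable 2 to 4 h after a dose. If humans resemble this, the planned ratio falls visibly and does nearly as well as the time-linearity ratio. This stands as to likelihood. It does not exclude the problem, because no human half-life is given, two metabolites of unknown half-life are also analysed, and Part C may dose twice daily.

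Second, a reader might infer that the documents show autoinduction. They do not. The signal is in vitro; the same section reports weak to modest CYP3A4 inhibition and stability in human hepatocytes, so the net direction and size of any effect are unknown.

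Third, half-life, CL/F and the Day 3 and Day 7 concentrations are summarised by day, so an attentive reader may notice a change. This stands in part. By-day CL/F understates the rise when drug accumulates, and half-life stays still if only bioavailability changes.

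A reader might also infer that the plan will declare absence of accumulation, that a wrong clearance will reach Phase 2, or that the ratio settles the contraception question. Neither document sets a rule for such a declaration. Protocol 1.2.3 foresees further interaction studies. Appendix 3 already treats hormonal contraceptives as not effective alongside TLC-2716, so any inference from this ratio would be indirect.

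**Conclusion.** The point holds as a gap in the SAP. Its only formal time comparison cannot by itself separate accumulation from a change in clearance, and the protocol's CLss/F and Ctau are missing from its parameter table. Whether this matters depends on a half-life that the documents do not give. A ratio near 1 despite a clearance rise of 25% or more needs roughly 10 h or more once daily, or 5 h or more twice daily, for the parent or a metabolite. At about 4 to 6 h or less the planned ratio would itself fall below 1. In between, the loss is one of sensitivity: 0.51 against 0.80 at 8 h and θ = 1.5.

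These figures rest on one compartment, steady state by Day 14 and the assumed CVs. Autoinduction is a reason to plan for the comparison, not an established fact about the drug.

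**What to change.** 1. Restore CLss/F = dose/AUCtau(Day 14), and Ctau, to SAP 8.1.3.
2. Add to SAP 8.1.6 the ratio AUCtau(Day 14)/AUCinf(single dose) on the log scale with 90% CI: within subject where Day 1 AUCinf is estimable, otherwise against Part A at the same fed dose. Do not substitute AUC(0-24) for AUCinf unless little AUC lies beyond 24 h; once daily, that substitute is the accumulation ratio again. Do the same for metabolites where applicable, using the AUC ratio only.
3. State that the accumulation ratio is read against R predicted from single-dose half-life, not against 1. Summarise Day 3, 7 and 14 pre-dose levels descriptively. A Day 14 versus Day 7 test would not serve, since it misses induction complete by Day 7.
4. Reconcile the end of Day 1 MAD sampling between protocol 6.5.1 with both schedules (12 h) and SAP 8.1.2 (24 h), and state how Day 1 AUCtau is obtained.
5. State the precision of the Part A comparison per dose, and label any figure pooled over doses as assuming one common ratio.

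Items 1 to 3 and 5 cost SAP text and one extra model on samples already scheduled. Item 4 needs the two documents aligned.
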